### Identifying optimal intervention timing to enhance SPSRS intervention's efficacy

If SPSRS proves efficacious in reducing StD's depressive symptoms, estimating its appropriate intervention duration is crucial, especially because its video‐viewing time has not yet been sufficiently established. Identification of appropriate intervention duration not only enables theoretical refinement of the therapeutic mechanism and SPSRS process but can also help clarify its clinical implementation. Therefore, the trial's secondary objective is to explore an appropriate intervention duration.

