### Sample size

In the previous 5‐week pilot RCT, Hedge's g for CES‐D scores between the SPSRS and control groups was 0.61.^25^ However, pilot studies have been shown to overestimate results.^34^, ^35^, ^36^ Therefore, considering a Hedge's *g* of 0.4, a two‐sided significance level of 5%, and a power of 80%, the sample size was calculated at 100 participants per group, totaling 200. Furthermore, internet‐based studies have reported dropout rates of 30%, and a systematic review of RCTs in smartphone apps for depression indicated a dropout rate of 47.8% after adjustment for publication bias.^70^, ^71^ Therefore, assuming a 50% dropout rate, this trial's sample size, using the pwr package in R (version 4.5.1), was calculated at 200 participants per group, totaling 400.

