#### Estimating appropriate intervention time for SPSRS

The estimation of the appropriate SPSRS intervention time will use data from the experimental group. Each participant's reliable change (RC) in depressive symptoms will be defined as a change in the CES‐D score (baseline to 5 weeks) that exceeds the minimal important change (MIC). The appropriate SPSRS video‐viewing time will be estimated by the receiver operator characteristic (ROC) method, which calculates the area under the curve, sensitivity, specificity, and the Youden index.^76^ The maximum Youden index point will be the optimal SPSRS intervention time. A previous study has estimated the CES‐D score's MIC; however, the MIC may vary depending on the disease, the intervention, the follow‐up period, and the estimation method.^77^, ^78^, ^79^ Therefore, the CES‐D score's MIC used as this trial's RC will be estimated using a predictive modeling method anchored to the GRC scales after the experimental group's 5‐week intervention.^78^, ^79^ The ROC method will be implemented with the pROC package, and the predictive modeling method will be conducted with the stats package.

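### The viewing-time rule labels the maximum Youden point the optimal time with no condition on the AUC, so it names a time even when viewing time is unrelated to improvement

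*Protocol article*

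**What the plan says.** The Introduction (Identifying optimal intervention timing to enhance SPSRS intervention's efficacy) motivates the question conditionally: "If SPSRS proves efficacious in reducing StD's depressive symptoms, estimating its appropriate intervention duration is crucial". It then states the aim without a condition: "the trial's secondary objective is to explore an appropriate intervention duration".

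The analysis is set out under Statistical analysis, Estimating appropriate intervention time for SPSRS. It has one arm: "The estimation of the appropriate SPSRS intervention time will use data from the experimental group". Each participant is classed as improved or not according to whether the CES-D change exceeds a minimal important change estimated within the trial. Viewing time is then related to that class by the ROC method, "which calculates the area under the curve, sensitivity, specificity, and the Youden index". The decision rule follows: "The maximum Youden index point will be the optimal SPSRS intervention time". The section gives no result under which no time would be named.

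**The concern.** The Youden index at a cut-point is sensitivity plus specificity minus 1. It is zero at both ends of the ROC curve, so its maximum is never below zero and always sits somewhere, even when the true AUC is 0.5. A rule that equates that location with an optimum cannot return a negative answer.

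The single-arm design adds to this. Participants enter with a CES-D score of 16 or more, so some will improve through natural course or regression to the mean, and they count as responders exactly as those helped by the intervention do.

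Even where viewing time does matter, the maximum Youden point is the value that best separates responders from non-responders. That need not be the duration with the greatest benefit.

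At stake is what the secondary objective can conclude. The Introduction hopes that the answer will help clarify clinical implementation, and a figure labelled optimal will be read in that light.

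**Working it through.** **1. Number of participants available.** Inputs from Sample size: "considering a Hedge's *g* of 0.4", two-sided 5% level, 80% power, 50% dropout.
- Normal approximation: n = 2(1.960 + 0.842)² / 0.4² = 2 × 7.85 / 0.16 = 98.1, so 99 per group.
- t-test solution: 99.08, so 100 per group. Power at 100 is 80.4%.
- Dropout: 100 / (1 − 0.5) = 200 per group.

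The plan's figures reproduce. The ROC analysis would therefore have about 100 experimental completers, or 200 with no dropout.

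**2. The rule when there is no relation.** Viewing time was generated independently of improvement and the stated rule applied (5,000 runs per setting). Assumptions not in the document: 20%, 30% or 50% improved; log-normal viewing time with median 350 min and log-SD 0.5. The median was set at the minimum total viewing time given under Interventions.

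| | n = 100 | n = 200 |
|---|---|---|
| Maximum Youden above zero, longer viewing fixed as favourable | 99.0% | 99.5% |
| Mean maximum Youden, same direction | 0.115 to 0.149 | 0.083 to 0.105 |
| Mean maximum Youden, direction taken from the data | 0.164 to 0.208 | 0.118 to 0.148 |
| Central 95% of AUC estimates, 50% improved | 0.39 to 0.61 | 0.42 to 0.58 |

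When the direction is taken from the data, the maximum is above zero in 100% of runs. Youden and AUC values depend only on ranks, so these rows do not depend on the assumed shape of a continuous viewing-time distribution.

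**3. The minutes that would be named with no relation.** These do depend on the assumed distribution (n = 100, longer viewing fixed as favourable, 5th to 95th percentile):
- gamma, mean 350 and SD 150: about 145 to 620 min;
- log-normal as above: about 155 to between 780 and 825 min;
- viewing heaped at the 350-min target: 45 to 418 min.

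In each case the range spans several hundred minutes.

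**4. The rule when there is a relation.** Assumptions: gamma mean 350 and SD 150, maximum benefit 6 points, SD of change 8, improvement threshold 4, n = 100.
- Step benefits starting at 200, 350 and 500 min give median cut-points of 246, 349 and 438 min. The rule does respond to a true threshold, though the cut-points for the outer two steps are pulled towards the middle.
- Gradual benefits, complete at 350 min or still rising to 700 min, give a mean AUC of about 0.57. That lies inside the 0.39 to 0.61 range expected with no relation at this sample size, so one trial of this size could not reliably tell such a relation from none.

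**5. Effect of an AUC condition.** Requiring the lower limit of a two-sided 95% interval for the AUC to exceed 0.5 lets through about 2.5% of no-relation data sets by construction (2.8% in simulation), against essentially all of them under the rule as written. It passes in about 20 to 26% of data sets under weak relations and about 70% under a clear step at 350 min.

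**The case against.** **The aim is exploratory, and the AUC will be calculated.** Both are true, and they limit the seriousness. A reader who sees an AUC near 0.5 can discount the cut-point. But the stated rule attaches the label whatever the AUC is.

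**AUC criteria and bootstrap intervals belong in an analysis plan that is not shown.** Their absence alone would be no finding. The point rests on a rule that the article states outright.

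**The Introduction already supplies the efficacy condition.** This largely stands. A reader might infer that the plan intends to report an optimal time even after a null primary result. The document does not clearly support that, because the opening conditional can fairly be read as governing the objective. What remains is that neither the objective nor the rule repeats it. Nor would it resolve the main problem: the intervention could work while viewing time, over the range observed, says nothing about who improves.

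**A further inference to avoid.** A reader might conclude that the cut-point is nearly the same whatever the true dose-response, or that it mainly reflects how long people happened to watch. The calculations do not support this. The step scenarios move the cut-point. With gamma viewing times of mean 250 and SD 220, gradual benefits complete at 100 min, complete at 350 min or rising to 700 min give median cut-points of 113, 193 and 229 min. Under mean 350 and SD 150, the 100-min case resembles no relation only because about 1.2% of participants watch less than that (mean AUC 0.50).

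**Reporting the estimate with its uncertainty and no gate is also defensible.** That is fair for an exploratory aim, but it still requires the interval and a neutral label.

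**Conclusion.** The point holds in a limited form. As written, the rule cannot conclude that no informative viewing time was found. With no relation and about 100 completers it names a time in essentially every data set, with a mean maximum Youden index of about 0.11 to 0.15 arising by chance. The Youden figures rest on the assumed share improved (20 to 50%) and on the plan's own dropout rate. The minute ranges rest on assumed viewing-time distributions and only illustrate scale.

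The mismatch with the Introduction is one of wording and is secondary. The primary comparison, its error rate and the sample size are untouched. The change is still worth making, because it alters what the secondary objective can legitimately report. No view is taken on what the viewing time should be.

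**What to change.** In Estimating appropriate intervention time for SPSRS:
1. Name a viewing-time cut-point only if the lower 95% limit of the AUC exceeds 0.5, with the direction fixed in advance as longer viewing meaning improvement. Otherwise report that no threshold was identified.
2. Give any cut-point with a bootstrap 95% interval.
3. Call it *the cut-point that best separates responders*, and drop the description of it as optimal.
4. Restate the Introduction's efficacy condition so that the two sections agree.

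The cost is a few sentences and a bootstrap. The real downside is the low pass rate of the AUC condition under a modest relation (step 5 of the working): the trial may well report no threshold when one exists. Recruitment is planned to run to March 2030 and no interim efficacy analysis is planned, so an amendment can precede the outcome analysis.

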### Data management, access to data, and confidentiality

Data entry and statistical analysis will be performed using Kurashiki Heisei Hospital computers unconnected to the Internet. Data from market research companies can be downloaded by logging on to the company websites. An ID and password are required to enable login, which will be sent only to the research manager by the market research company. Furthermore, data downloads are available for 30 days, after which the data will be deleted and downloads no longer possible. Survey data are provided in an anonymized state with participant numbers assigned. Additionally, no information regarding participants' identities will be provided or entered into an electronic database. All participant data will be entered into an Excel database stored on a USB drive equipped with password protection and encryption (AES‐256) and stored in a lockable cabinet at Kurashiki Heisei Hospital to maintain confidentiality. Additionally, USB memory passwords will be managed in a separate locked cabinet to prevent incidents such as information leaks or loss. In the event of a data breach or loss, the content of the breach and its potential impact shall be promptly investigated. The findings shall be reported to the Ethics Review Committee of Kurashiki Heisei Hospital, which will determine the appropriate response. Cross‐sectional data will be periodically sent from the survey company to Kurashiki Heisei Hospital. After the research team's error checking, these data will be cumulatively added to the previous data.

To ensure the entered data's accuracy, three researchers will conduct a two‐step verification. First, two researchers will independently enter data into Excel spreadsheets. To verify consistency, the third researcher will then compare the data sent by the research company with the two previously entered datasets. Only the data manager and principal investigator have database access, and they will complete the statistical‐analysis dataset. Changes and updates to these databases will be recorded and monitored using Windows Event Viewer and Excel history functions. In accordance with the principles of role‐based access control, only data managers and principal investigators possess database access rights, and they will finalize the datasets for statistical analysis. At this time, there are no plans to release the datasets to third parties. Furthermore, no secondary analyses are currently scheduled. However, if access to the data is requested for purposes such as secondary analysis or meta‐analysis, it will be granted only after obtaining renewed approval from the ethics review committee (in addition to any third‐party ethics committee) and renewed informed consent from the participants. All this study's obtained information will be stored at Kurashiki Heisei Hospital for 10 years.

### Data monitoring

Video‐based interventions are non‐invasive and are not expected to cause serious harm. In fact, there have been no reports of AEs resulting from the use of SPSRS by individuals with StD. Furthermore, since data collection will be conducted using an online survey, there are currently no plans to establish a formal data monitoring committee or to conduct an interim analysis of intervention efficacy or trial monitoring.

### Adverse events and post‐trial care

Multiple studies have examined SPSRS as a treatment for StD using the same 5‐week intervention period, and none have reported serious AEs, such as the onset of MDD.^16^, ^24^, ^25^, ^29^ Nonetheless, the possibility of such adverse effects on participants' physical and mental health should never be discounted during clinical trials. Therefore, we will employ methods similar to those used in previous studies to systematically monitor the occurrence and signs of AEs and respond promptly.^24^, ^80^ AEs are considered signs of deteriorating mental or physical health, regardless of whether the individual participates in the SPSRS‐based intervention. Participants will be encouraged to consult with the chief investigator if they notice any signs of deterioration in their mental or physical health during or after the trial. Furthermore, monitoring for serious AEs will continue after trial completion. To ensure prompt and appropriate handling of AEs occurring after trial completion, participants may contact the research team for up to one month after the final survey. This information will be conveyed to each participant during the electronic informed consent process. If an AE is reported, the research team will evaluate and document the nature, duration, severity, and outcome, as well as the participant's relationship to the study. Any AEs will be immediately reported to the Kurashiki Heisei Hospital Ethics Review Committee, which will decide whether the study should be continued, modified, or discontinued. Additionally, the research team will contact all participants and strongly recommend that they utilize relevant health services and consult mental health professionals if needed. Medical expenses related to AEs will not be covered as harm beyond that typically associated with the care provided in this trial is considered extremely unlikely.

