### Data collection

Table 1 shows the outcome assessments' schedule. Information regarding depressive symptoms (primary outcome), psychological distress, and anxiety symptoms will be collected at baseline, 3 and 5 weeks after the intervention begins. Additionally, as a baseline assessment, demographic data will be collected via online questionnaires: gender and age, lifestyle characteristics including sleep duration and exercise, drinking, and smoking habits. To protect users' privacy, the research team will not track the specific video content viewed by participants. Instead, only participants' video‐viewing time will be collected using the SPSRS video‐viewing time recording site managed by the principal investigator. To prevent missing data, the questionnaires are set to reject incomplete responses automatically.

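### Adverse-event monitoring is called systematic, but only participant-initiated reporting is described and MDD onset is not reassessed after screening, so few or no reported events would be weak evidence of safety

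*Protocol article*

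**What the plan says.** All of the collection method is in the protocol article, section Adverse events and post-trial care. The stated aim is to "systematically monitor the occurrence and signs of AEs and respond promptly", using methods similar to those of two cited studies. The steps that follow are:

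- During and after the trial: "Participants will be encouraged to consult with the chief investigator if they notice any signs of deterioration in their mental or physical health".
- After the trial: "participants may contact the research team for up to one month after the final survey".
- Trigger for evaluation: "If an AE is reported, the research team will evaluate and document the nature, duration, severity, and outcome".

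The definition is broad: "AEs are considered signs of deteriorating mental or physical health", whether or not the person takes part in the SPSRS intervention. On earlier SPSRS studies the section says "none have reported serious AEs, such as the onset of MDD".

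Under Data collection, "Information regarding depressive symptoms (primary outcome), psychological distress, and anxiety symptoms will be collected at baseline" and again at weeks 3 and 5. Study setting and recruitment timeline lists the surveys in order: CES-D, K6 and GAD-7 at week 3, and the same three plus the GRC at week 5. The PHQ-9 serves eligibility, and the limitations in the Discussion place the MDD assessment before the trial. Data monitoring plans no formal committee and no trial monitoring. It gives as reasons the non-invasive nature of the intervention, the absence of adverse-event reports so far, and online data collection.

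**The concern.** A systematic method asks every participant the same question at the same times. The method described waits for a panel member to notice a problem, connect it with the trial and contact the investigator. The number of events then depends on willingness to report as well as on how many occurred.

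Three things are at stake. First, the absence of earlier reports is one of the reasons for having no monitoring committee, and a low count here could be read in the same way. Second, the safety route under Trial stopping rules depends on events reaching the Ethics Review Committee. On the stated route, that requires a participant to volunteer them. Third, the Introduction and Discussion justify the trial partly by prevention of MDD, yet MDD status by arm at week 5 would be unknown.

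Reporting might also differ between arms. The experimental arm receives a link, instructions and a weekly reminder, and no comparable contact is described for the waiting list. That is an inference from the design; the documents do not state it.

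**Working it through.** **1. Promise against method.** Of the three steps quoted above, the first two are initiated by the participant and the third depends on them. No step has the team asking.

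**2. Could the planned surveys detect MDD onset?** Under the rule in Exclusion criteria, a CES-D score of 16 or higher applies to both subthreshold depression and MDD, and only the PHQ-9 items separate them. The CES-D at weeks 3 and 5 therefore cannot identify MDD by the protocol's own definition. The PHQ-9, which can, is not in either follow-up list. Table 1 is not shown, but the text gives the schedule.

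**3. What the surveys do hold.** CES-D, K6 and GAD-7 at both visits, and GRC options 4 and 5 (slightly or a lot worse) at week 5, are signs of deterioration collected identically in both arms. No section says they count as adverse events or will be tabulated as such.

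**4. How informative is a zero count?** The documents state no adverse-event or MDD rate, so the only figure to reproduce is the sample size. With g = 0.4, two-sided 5% and 80% power, the t-test needs 99.08 per arm, rounded up to 100. With 50% dropout, 100 / 0.5 = 200 per arm. This agrees with the protocol.

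Let p be the true 5-week risk and f the share of events that participants report themselves (both assumptions), with N = 200 in one arm.

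The upper 95% bound on p after zero reports solves (1 − p·f)^N = 0.05, so p = (1 − 0.05^(1/N)) / f. For N = 200, 1 − 0.05^(1/200) = 0.01487.

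| f (assumed) | Bound on p after zero reports among 200 |
|---|---|
| 1 | 0.01487 / 1 = 1.5% |
| 0.5 | 0.01487 / 0.5 = 3.0% |
| 0.25 | 0.01487 / 0.25 = 5.9% |

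The probability of no report in the arm is (1 − p·f)^200:

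| p (assumed) | f = 1 | f = 0.5 | f = 0.25 |
|---|---|---|---|
| 1% | 0.13 | 0.37 | 0.61 |
| 2% | 0.02 | 0.13 | 0.37 |
| 5% | <0.001 | 0.006 | 0.08 |

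A lower reporting share makes a zero count more likely and less informative, but not certain.

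**5. Effect of dropout.** A survey item is answered only by those who complete the survey. At the planned 50% dropout that is 200 × 0.5 = 100 per arm, and zero events among them bound the risk at 1 − 0.05^(1/100) = 3.0%. This is about the same as zero spontaneous reports among 200 with half of events reported. On this measure a solicited item gives a tighter bound when fewer than half of events would be volunteered. In any case its denominator is known, which is not so for spontaneous reports.

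**The case against.** The strongest reply is that part of the method is out of view. The article refers to two cited studies for its adverse-event methods, condenses a fuller protocol, and has a schedule table that is not shown. An active question may exist there. This stands as a limit on the point. It does not remove the mismatch in the text, which promises systematic monitoring and then describes only passive reporting.

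A second reply is that deterioration is measured in both arms by the scales already planned. That is right, and it makes the fix smaller. But the article does not connect those data to its adverse-event definition.

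A reader might infer more than the documents support:

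- **That a finding of no adverse events is built in.** It is not. Participants can report, all are told at consent how to do so, and the second table shows that a zero count can be unlikely under plausible-looking inputs. The protocol also plans no such conclusion for this trial: its statements about absent events concern earlier use of SPSRS, and Outcomes lists no adverse-event or MDD outcome.
- **That MDD onset is the only serious event named.** It is introduced as an example.
- **That reporting will differ by arm.** The extra contact described is an emailed link with instructions and one templated weekly reminder. A difference is possible, not shown.
- **That the number of missed events can be estimated.** No onset or reporting rate is given. The Discussion places frequent progression to MDD at 1 to 3 years after baseline, which gives no 5-week rate.

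Repeating the PHQ-9 at week 5 is not free either. The Discussion says that the research company's terms prevent the team from offering resources to candidates who report suicidal ideation on it. A second administration would raise the same problem in enrolled participants.

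**Conclusion.** The point holds as a mismatch between the claim of systematic monitoring and the passive route described, together with the absence of any MDD assessment after screening. Few or no reported events would be weak evidence of safety, and a comparison between arms may not be like with like.

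The size of the under-count is unknown. The illustrative bounds of 1.5%, 3.0% and 5.9% rest on assumed reporting shares of all, half and a quarter of events among 200 participants. They show the direction and scale of the lost information, not an estimate for this trial. The efficacy analysis is unaffected. This is an inexpensive improvement worth making before recruitment is far advanced, and the conclusion would change if the full protocol already asks about adverse events at weeks 3 and 5.

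**What to change.** Add one fixed adverse-event item, worded identically in both arms, to the automated surveys at weeks 3 and 5. Report by arm, with the number responding as denominator, both the solicited events and worsening on the scales already collected, for example CES-D increase from baseline and GRC responses 4 and 5. Keep spontaneous reports and list them separately.

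The cost is a minute or less per participant and some extra reports for the team to evaluate. Tabulating the existing scales needs no new data.

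Repeating the PHQ-9 at week 5, scored by the screening rule, is optional. It would give MDD status by the protocol's own definition, but the sponsor must weigh it against the restriction on responding to suicidal-ideation answers. What should follow a detected deterioration is also for the sponsor to decide.

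If no active item is added, remove the word systematically and state that the absence of reported events does not show absence of harm or of MDD onset.
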